## Abstract

**Introduction:**

The current understanding of colorectal carcinogenesis is based on the adenoma-carcinoma sequence, where genetics, intestinal microbiota changes and local immunity shifts seem to play the key roles. Despite the emerging evidence of dysbiotic intestinal state and immune-cell infiltration changes in patients with colorectal adenocarcinoma, early and advanced adenoma as precursors of colorectal cancer, and carcinoma *in situ* as the following progression, are rather less studied. The newly colon-site adapted AI-based analysis of immune infiltrates is able to predict long-term outcomes of colon carcinoma. Though it could also facilitate the pathologic evaluation of precancerous lesion’s potential to progress. Therefore, the purpose of this prospective cohort study (MIMICA-1) is, firstly, to identify the intestinal microbiota and immune infiltration patterns around the normal bowel tissue, early and advanced adenoma, carcinoma in situ, and adenocarcinoma, and secondly, to analyze the immune – microbiome interplay along the steps of conventional colorectal tumorigenesis.

**Methods and analyses:**

This study aims to prospectively recruit 40 patients (10 per group) with confirmed colorectal dysplasia undergoing endoscopic polypectomy, endoscopic mucosal resection for colorectal small (≤1cm), and large (>1cm) adenoma or carcinoma in situ, or biopsy and subsequent colon resection for invasive colorectal cancer, and 10 healthy patients undergoing screening colonoscopy. Stool samples will be collected prior to bowel preparation for the analysis of fecal (luminal) microbiota composition. Biopsy specimens will be taken from the terminal ileum, right colon, left colon, and a pathological lesion in the colon (if present) to assess mucosa-associated microbiota composition and intestinal immunity response. DNA will be extracted from all samples and sequenced using the Illumina MiSeq platform. Unifrac and Bray-Curtis methods will be used to assess microbial diversity. The intestinal immune system response will be examined using digital image analysis where primarily immunohistochemistry procedures for CD3, CD8, CD20 and CD68 immune cell markers will be performed. Thereafter, the count, density and distribution of immunocompetent cells in epithelial and stromal tissue compartments will be evaluated using AI-based platform. The interaction between the microbial shifts and intestinal immune system response in adenoma-carcinoma sequence and the healthy patients will be examined. In addition, fecal samples will be explored for gut microbiota’s composition, comparing fecal- and tissue-derived bacterial patterns in healthy gut and along the adenoma-carcinoma sequence.

**Discussion:**

We hypothesize that changes within the human gut microbiota led to detectable alterations of the local immune response and correlate with the progression from normal mucosa to colorectal adenoma and invasive carcinoma. It is expectable to find more severe gut immune infiltration at dysplasia site, though analyzing invasive colorectal cancer we expect to detect broader mucosa-associated and luminal microbiota changes with subsequent local immune response at near-lesion site and possibly throughout the entire colon. We believe that specific compositional differences detected around premalignant colorectal lesions are critically important for its primary role in initiation and acceleration of colorectal carcinogenesis. Thus, these microbial patterns could potentially supplement fecal immunohistochemical tests for the early non-invasive detection of colorectal adenoma. Moreover, AI-based analysis of immune infiltrates could become additional diagnostic and prognostic tool in precancerous lesions prior to the development of colorectal cancer.

**Registration:**

The study is registered at the Australian New Zealand Clinical Trials Registry (ACTRN12624000976583) https://www.anzctr.org.au/.

## Introduction

1

Colorectal cancer (CRC) represents the third most common cancer and is the second-leading cause of cancer-related deaths worldwide (1, 2). The exact etiology of CRC remains unclear, although several studies have focused on the evaluation of the mechanisms involved. Most CRC cases (approximately 90%) occur sporadically (not related to the genetics of family with history of the disease), and several lifestyle factors including obesity, diet with a high content of fat and/or red and/or processed meat, environmental pollutants, cigarette smoking, and alcohol abuse, have been associated with CRC development and progression (2–4). Furthermore, there is emerging evidence that patients with CRC display significant alterations in gut microbiota, mainly characterized by an increase in opportunistic pathogens (e.g., *Enterococcaceae*, *Campylobacter*) (5, 6) and a decrease in butyrate-producing bacteria, including *Bifidobacteria*, *Roseburia* and *Faecalibacterium prausnitzii* (5–8). Overall, these alterations in the gut microbiome have been proposed to play an important role in tumor formation and progression (8–11).

As the initial genetic composition of all cells of a single human is identical, it is fairly questionable why the cells of the distal small bowel have 200 times reduced risk of cancer, when compared to the proximal large bowel (12–14). On the one hand, embryological development of human gastrointestinal tract through foregut, midgut and hindgut structures may play the most significant role. Whilst the right and proximal two-thirds of the transverse colon are midgut structures like the majority of the small intestine, the remaining distal colon and rectum are embryologically formed from the hindgut (15). Therefore, structurally, functionally and, in general, ontogenetically small and large intestines are different organs. Nevertheless, the role of continuous presence of microbes and decreasing immune cell infiltration towards distal large bowel cannot be diminished (16). Particularly, the composition of site-specific (luminal, and especially, mucosa-associated) bowel microbiota, along with the changes in local immune response have been discovered to have direct and indirect implications on anti- and procarcinogenic act in the gut (16–18).

With the expansion of research in the field of the human microbiome and immunomodulatory effect of microbiota, the immune – microbiome interplay in CRC began to be more precisely assessed (17, 18). Tumor – infiltrating lymphocytes (TILs) and their distributions within tumor microenvironment (TME) compartments have been reported as potential prognostic and predictive biomarkers in various cancer types, including CRC (19). The count, density, and distribution of immunocompetent cells (e.g. CD3, CD8, CD20, CD68 and CD163, FOXP3; CD8/CD20 Immunogradient or Immunoscore) in epithelial and stromal compartments are being used for the evaluation of host local-intestinal immune system response in cancerous colorectal tissues (20–22). Studies of local gut immunity highlight its practical importance in terms of CRC treatment (immunotherapy), as well (23). Currently developed digital image analysis (DIA) tools and spatial analytics increase the accuracy and precision of TILs measurements. It can also enable the analysis of subvisual cell distribution patterns that all together improve the informative power of immune response profiling and the extraction of novel indicators (22, 24). Moreover, recently the prognostic models that integrate local immune response and histopathological features have shown additional value predicting CRC outcomes (20, 21, 25). Similarly, the combinatorial analysis of the immune system – microbiome interaction in the context of pathology and genetic alterations is likely to reveal new insights into adenoma – carcinoma development (26–28).

Several studies found that changes in the gut microbiota manifest in disease progression as a result of epigenetic modification in the host, which in turn influences the differentiation and function of immune cells adversely (27, 28). CRC was also shown to be associated with higher levels of oncogenic mutations, such as K-ras, COX2, c-MYC and p53 (27–29). Accumulation of these genetic changes within colorectal epithelial cells is a basis of the current understanding of adenoma-carcinoma sequence. However, the interplay between the three components – genetics, immunity, and gut microbiota compositional shifts – are not yet studied sufficiently (30). To the best of our knowledge, our study would be one of the first to concurrently examine the relation of microbial, histologic, and local immune changes in the progression of colorectal adenoma to cancer.

### Aims of the study

1.1

We expect to advance the knowledge of CRC pathogenesis by studying the changes of the microbiota structure around early, advanced adenoma, carcinoma *in situ* and CRC, and comparing them to the microbiota of the distal small bowel wall and the stool microbiota of the same person and other healthy patients (healthy controls). Apart from microbiota analysis, we also aim to determine the immune infiltration patterns of the area around adenoma and carcinoma and compare them to the healthy segments of the same person’s distal small and large bowel, as well as to the bowel wall immune-cell infiltrates of the healthy controls. The latter will be performed by employing the AI-based digital image analysis, which is currently being used in predicting colorectal cancer outcomes (20–22). In addition to this, in our study the AI-based DIA will be used to describe premalignant dysplastic colorectal lesions and normal bowel wall structures. Hopefully, this deep-learning image processing technique could be a promising tool for the pathologic evaluation of precancerous lesion’s capacity to progress.

Hypothetically, if relevant differences were found between microbial composition and immune changes, the samples collected during this study would be further explored to evaluate whether they correspond to the growing collection of genetic abnormalities leading to the development of CRC.

Sample collection is another challenging step in human gut microbiota studies. Many studies on the gut microbiota, including those related to CRC, are conducted using fecal samples, since its collection is an easy, non-invasive and repeatable procedure (31, 32). Thus, while fecal samples represent a powerful strategy for finding diagnostic and prognostic biomarkers, tissue samples (from colonic mucosa and dysplastic changes) may be more valuable to disentangle the physiopathology of CRC (6, 33, 34). Accordingly, in our study, we aim to investigate the difference between fecal- and tissue-derived gut bacterial compositions and their role in human bowel microbiota studies in order to increase sampling accuracy and applicability.

In addition, while performing this study, we would advance the knowledge on the dynamics of the normal bowel microbiota and on the normal local immune system of the distal small and large bowel.

### Objectives and tasks of the study

1.2

The primary objective of the study is to identify the gut microbiota and immune infiltration patterns around normal bowel tissue, early adenoma, advanced adenoma, carcinoma *in situ* and invasive carcinoma.

The secondary objectives of MIMICA-1 are to investigate whether intestinal microbiota correlates with local immune response, and to compare mucosa-associated and fecal-derived microbiota compositional changes in healthy patients and along the adenoma-carcinoma sequence.

The aim will be achieved by performing the following tasks within the study:

To evaluate the normal microbiota of the distal small bowel, the right side of the large bowel and the left side of the large bowel and correlate the microbiota of the bowel wall to the stool microbiota;To determine the microbiota of the early (<1cm) adenoma, advanced (>1cm) adenoma, carcinoma *in situ* and invasive carcinoma and to compare it to the microbiota of the normal bowel as well as in the healthy segments of the small and large bowel;To study the normal immune infiltration (in the form of count, density and distribution of immunocompetent cells in epithelial and stromal tissue compartments) of the normal small and large bowel and to correlate it to the normal bowel wall and stool microbiota;To compare the normal immune infiltration to the immune infiltration around the early (<1cm) adenoma, advanced (>1cm) adenoma, carcinoma *in situ* and invasive carcinoma of the large bowel;To identify, whether changes in microbiota and immune environment interrelate and correlate with the progression of the dysplastic changes within the epithelium of the large bowel;To collect and contain colon mucosal biopsies in a biobank for further examination of intestinal epithelial cell oncogenic mutations and its correlation between gut microbiota’s compositional changes and the response of the intestinal immune system in the healthy small bowel and colon mucosa, and across adenoma-carcinoma sequence (in simple CR adenoma (< 1 cm); advanced CR adenoma (≥ 1 cm), Ca *in situ* and CRC).

## Methods and analysis

2

### Study design

2.1

#### Setting

2.1.1

The present trial (MIMICA-1) is an open prospective observational cohort study conducted in a tertiary high volume expert Center for Abdominal and Onco-Surgery and Hepatology, Gastroenterology and Dietetics Center at the Vilnius University Hospital Santaros Klinikos, Vilnius, Lithuania.

#### Approvals

2.1.2

The study protocol was reviewed and approved by an independent Vilnius Regional Bioethics Committee (Lithuania) in April 2022 (internal No.: 2022/4-1422-902) and registered at web-based Australian New Zealand Clinical Trials Registry (ACTRN12624000976583) https://www.anzctr.org.au/ in July 2024. No significant protocol changes or deviations will be allowed without documented approval.

The study will be carried out in accordance with the principles of the Declaration of Helsinki and Strengthening the Reporting of Observational Studies in Epidemiology (STROBE) statement (35). A STROBE checklist (**Supplementary Table 1**) and a SPIRIT checklist (**Supplementary Table 2** and **Figure 1**) are attached.

**Figure 1 f1:**
[figure not shown]
Flow diagram of the study. CR, colorectal; Ca in situ, carcinoma *in situ* (carcinoma in adenoma/intramucosal carcinoma); adenoCa, adenocarcinoma; IHC, immunohistochemistry; DIA, digital image analysis; BBPS, Boston Bowel Preparation Scale.

#### Consent

2.1.3

Patient informed written consent for participation will be obtained by the specialist or project’s researcher prior to inclusion in the study. A member of the team will inform patients of the objectives and methodology of the study and patients will be given a written patient information sheet. Patients consent to have their stool samples and intestinal tissue specimens collected and subsequently analyzed for microbiota composition and local immune infiltration. Additionally, participants consent to have collected tissue specimens stored at a biobank for up to 5 years for future genetic analysis of specific oncogenic mutations affecting the progression of colorectal adenoma. Patients will be able to ask any questions regarding participation in the study. Participants may withdraw or revoke consent at any time without giving explanations and without any prejudice to them. No financial incentives will be provided to any of the participants.

### Study population

2.2

Adult patients (from 18 years old) who will be referred for a colonoscopy either through the bowel cancer screening program, or as a part of a surveillance program, or due to symptoms and diagnosed with histologically confirmed colorectal dysplasia (exposure groups) or adult patients without any polypoid lesions found during the colonoscopy (control group). It is expected that most of the participants will be referred due to iron deficiency anemia, altered bowel habits, weight loss, rectal bleeding, planned polypectomy, CRC-associated family history, abnormal imaging, or polyp surveillance.

#### Eligibility criteria

2.2.1

##### Inclusion criteria for exposure groups

2.2.1.1

Patients with histologically confirmed dysplastic colorectal lesion: early and advanced-adenoma, carcinoma *in situ* or adenocarcinoma. Advanced adenomas are defined as those with high-grade dysplasia, villous or tubulovillous histology, or a diameter ≥1 cm;Adult patients (≥18 years);Written informed consent.

##### Inclusion criteria for control (healthy) group

2.2.1.2

Healthy patients (without any polypoid lesions found during screening colonoscopy);Adult patients (≥18 years);Written informed consent.

##### Exclusion criteria

2.2.1.3

Patients under the age of 18 years;Confirmed serrated (sessile serrated (SSA), traditional serrated adenomas (TSA)) or hyperplastic polyps or non-polypoid lesions;Signs of colorectal tumor obturating the lumen of the bowel which would limit complete colonoscopy;Suffer from other gastrointestinal tumors;Pregnancy;Previous colon resection;History of surgery disrupting gastrointestinal tract integrity;History of inflammatory bowel disease (ulcerative, Crohn’s, radiation-induced, or infectious colitis or other previous chronic inflammatory illnesses);Familial adenomatous polyposis (FAP) or other hereditary colon syndromes;Clinically significant immunodeficiency;Evidence of infection;During the last year patient had:- suffered from *Cl. difficile* colitis or was a carrier of *Cl. difficile*; suffered from salmonellosis or other gastrointestinal infection;- a long-term (> 6 months) use or recently completed therapeutic antibiotic course within the last month;- corticosteroid and/or immunosuppressant therapy;- received chemo- or radiation therapy in the abdomen and/or pelvis chemotherapy;- regular use (> 3 months) of pre-/pro-/(sin)biotics and/or statins;- a long-term (> 6 months) use of proton pump inhibitors;Patients who cannot undergo colonoscopy on time and cannot cooperate fully.

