#### Questionnaires and physical evaluation

2.2.3

The personal information of the subjects will be conducted through the hospital’s indoor database and advanced health information questionnaires. Patients will be provided with questionnaires containing questions on demographics, anthropometric data (height, weight, body mass index (BMI) and waist circumference), health history, gastrointestinal disorders and interventional procedures, bowel symptoms, co-morbidities (including tobacco and alcohol consumption), use of certain medication (as antibiotics, probiotics, statins, proton pump inhibitors, corticoids and immunomodulators), dietary and ecological habits and possible microplastic intake. Physical evaluation will be assessed by the anesthesiologist on the procedure day.

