#### Pre-procedure

3.1.1

The collection of feces will be carried out prior to bowel preparation for colonoscopy or surgery (from 2 weeks until the planned procedure) at the residence. That way extensive alterations due to bowel cleansing in (only partially constant) individual intestinal luminal microbiota could be avoided. Briefly, participants will be instructed to, firstly, pass stool on the tray, secondly, dig up 1-3 spoons of stool and, thirdly, insert it into a sterile screw cap container. For reducing the change of microbiota composition in the stools, the liquid preservative will be added in each container sent to the preliminary participants. Patients will be asked to bring stool samples to the researcher at the hospital on the procedure day. Those with completed questionnaires, collected stool samples and written informed consent will eventually be enrolled in further study.

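### Exclusions for pre-/pro-/synbiotics, statins and proton pump inhibitors rest on duration of use alone, so a short-term user may still be taking the drug at sampling

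*Protocol article*

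**What the plan says.** Section 2.2.1.3 of the Protocol article introduces its drug-related exclusions with "During the last year patient had". The relevant lines are:

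- Pre-/pro-/synbiotics and statins: "regular use (> 3 months) of pre-/pro-/(sin)biotics and/or statins".
- PPIs: "a long-term (> 6 months) use of proton pump inhibitors".
- Antibiotics: "a long-term (> 6 months) use or recently completed therapeutic antibiotic course within the last month".
- Steroids and immunosuppressants: "corticosteroid and/or immunosuppressant therapy", with no minimum duration.

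Outside the one-year list, "Evidence of infection" is an exclusion in its own right.

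Section 2.2.3 has the questionnaire record "use of certain medication (as antibiotics, probiotics, statins, proton pump inhibitors, corticoids and immunomodulators". Section 3.1.1 has stool collected at home "from 2 weeks until the planned procedure"; biopsies are taken at the procedure (3.1.2). Section 4 plans a redundancy analysis of factors that shape the microbiome and does not name medication among them.

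**The concern.** Listing these drugs as exclusions shows that the sponsor regards them as unwanted influences on the microbiota. The antibiotic line shows that it also regards recency as relevant. For pre-/pro-/synbiotics, statins and PPIs, however, the only test is how long the drug was used during the year. Such a test can admit someone who is taking the drug when the sample is collected and turn away someone who stopped months before.

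The primary outcomes compare microbiota and immune infiltration between lesion groups and healthy controls, with about 10 patients per group. If current short-term use were unevenly spread over the groups, part of a difference in composition could reflect the drug and not the lesion stage. The secondary comparison of stool with tissue has a further exposure: a drug started after the stool sample and before the biopsies could affect one sample type and not the other.

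**Working it through.** The plan gives no figure on this point to reproduce. The check is to apply the eligibility wording literally to use histories.

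**Inputs.** Look-back of 12 months; threshold T = 3 months (pre-/pro-/synbiotics, statins) or T = 6 months (PPI), all from 2.2.1.3. Group size 10, from 2.2.4 and Table 2.

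**Assumptions.** The article does not say on which date the look-back ends; I take the sampling date. It does not say whether use before the look-back year counts; I count only use inside the year.

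**Rule.** Let s be the months before sampling at which use began and e the months before sampling at which it stopped (e = 0 if ongoing). Months counted = min(s, 12) − e. The patient is excluded if this exceeds T.

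| Use history | Months counted | T = 3 | T = 6 (PPI) |
|---|---|---|---|
| Ongoing, 2 months | 2 − 0 = 2 | eligible | eligible |
| Ongoing, 3 months | 3 − 0 = 3 | eligible | eligible |
| Ongoing, 4 months | 4 − 0 = 4 | excluded | eligible |
| Ongoing, 6 months | 6 − 0 = 6 | excluded | eligible |
| Ongoing, 7 months | 7 − 0 = 7 | excluded | excluded |
| Began 12, stopped 8 months ago | 12 − 8 = 4 | excluded | eligible |
| Began 12, stopped 5.5 months ago | 12 − 5.5 = 6.5 | excluded | excluded |
| Began 12, stopped 9 months ago | 12 − 9 = 3 | eligible | eligible |

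**Longest gap since stopping that still excludes.** 12 − e > T gives e < 12 − T: just under 9 months for T = 3 and just under 6 months for T = 6. If use before the look-back year also counted toward T, the gap could approach 12 months for both.

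**The other lines.** Any corticosteroid or immunosuppressant therapy in the year excludes, so current users are out. An antibiotic course finished within the last month excludes. An antibiotic course of 6 months or less that is still running is neither long-term nor finished, so the words do not name it; the separate infection exclusion may catch many such patients.

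**Timing.** Stool may precede the biopsies by up to 2 weeks. Section 3.1.2 states a procedure-day check on bowel preparation but none on medication.

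**Illustration only.** The share p of eligible patients who are current short-term users is not in the documents. If patients are independent, the chance of at least one in a group of 10 is 1 − (1 − p)^10:

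- p = 5%: 1 − 0.95^10 = 40%
- p = 10%: 1 − 0.90^10 = 65%
- p = 20%: 1 − 0.80^10 = 89%

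Each such patient is 10% of a group of 10. These figures show how readily a small group could contain a current user. They say nothing about the effect on the microbiota.

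**The case against.** The strongest reply is that a duration threshold is a legitimate choice aimed at established exposure. The article gives no data on how fast these drugs change the microbiota or how long a change lasts, so it cannot be shown from the document that a few weeks of current use matter more than sustained earlier use. That stands, and it rules out any claim about which exposure is stronger.

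A reader might infer that the drug exclusions as a whole ignore current use. They do not. Steroid and immunosuppressant therapy excludes at any time in the year, antibiotics have a one-month recency condition, and current users beyond 3 months (PPI: 6) are out. A site would also hardly admit a patient in mid-course when a course that has just ended excludes; the antibiotic gap is one of wording.

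A reader might also infer that symptomatic lesion patients start these drugs more often than controls, so that a drug effect would look like dysbiosis along the adenoma-carcinoma sequence. This is plausible but not shown. Section 2.2 lists screening, surveillance and symptoms as routes to colonoscopy, and its expected referral reasons cover most participants. Section 2.2.1.2 refers to screening colonoscopy for controls, but nothing says that controls are free of symptoms or that drug use differs by group. Lesion and own-control biopsies from one patient also share that patient's exposure, so those comparisons are less affected.

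Finally, medication is recorded, patients are re-checked for inclusion before being invited, and redundancy analysis could pick up a drug effect. This lessens the gap without closing it: medication is not named as a factor, and the group comparisons in section 4 are described without regard to it. Reference dates may well be in the full protocol, so their absence here is not itself a fault. The duration-only wording is what the article fixes.

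**Conclusion.** The point holds for two lines. For pre-/pro-/synbiotics and statins, ongoing use of up to 3 months is admitted at sampling, while a patient who stopped up to just under 9 months earlier can be excluded. For PPIs the corresponding limits are up to 6 months and just under 6 months. The antibiotic line needs only a word for ongoing courses. The steroid and immunosuppressant line is sound.

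The limits rest on a literal reading, a look-back that ends at sampling, and counting use inside the year only. Neither the size nor the direction of any bias in the between-group comparisons can be computed, because the share of current users, its spread over the groups and the drug effects are all absent from the document. This is an inexpensive improvement in participant selection, not evidence that the planned comparisons are invalid.

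**What to change.** Give the pre-/pro-/synbiotic, statin and PPI lines the kind of recency condition that the antibiotic line already has: use that is ongoing, or that ended within a pre-stated window before the stool sample. The protocol's own one month is an obvious candidate for that window. Add ongoing courses to the antibiotic line. On the procedure day, confirm that none of these drugs was started between stool collection and biopsy. The duration limits can stay beside the new condition.

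If the sponsor prefers not to exclude these patients, pre-state that the primary between-group comparisons and the stool-versus-tissue comparison will be repeated without current users, identified from the questionnaire.

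The cost is an eligibility amendment and one procedure-day question, or one repeated analysis. The first route loses a few short-term users to recruitment, which matters most for the carcinoma in situ group, where section 5.2 already expects too few cases. The second makes the repeated analysis slightly smaller. Both concern selection and analysis only and change no patient's medication.
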